**Methods:**

We use a stepped wedge cluster-randomized trial to evaluate implementation of LEAPS. Ninety-nine clusters will be randomized to receive the intervention in one of three 7-month steps (33 clusters/step). The primary outcome is children’s school readiness (indexed by the total score on the International Development and Early Learning Assessment (IDELA)). Secondary child outcomes are children’s IDELA domain scores and executive functions. Data are collected in cross-sectional surveys of 1089 children (11 children/cluster from 99 clusters) aged 4.5–5.5 years at four timepoints (baseline and at the end of each step). Additionally, we will enroll three non-randomized youth participant open cohorts, one per step (33 CYLs: 66 comparison youth per cohort; 99:198 in total). Youth cohorts will be assessed at enrollment and every 7 months thereafter to measure secondary outcomes of youth personal and professional development, depressive symptoms, and executive functions. A non-randomized school cohort of 330 LEAPS students (10 students/cluster from 33 clusters) will also be enrolled and assessed during Step 1 after intervention rollout and at endline. The quality of the learning environment will be assessed in each LEAPS ECCE center and in a comparison center at two timepoints midway following rollout and at endline. A concurrent mixed-methods implementation evaluation will assess program fidelity and quality, and the extent to which a technical support strategy is successful in strengthening systems for program expansion. A cost evaluation will assess cost per beneficiary. Data collection for implementation and cost evaluations will occur in Step 3.

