#### Youth participants

A case:comparison design will be employed in order to examine program impacts on youth participants. In each step, we will enroll an open cohort comprising the 33 CYLs from the 33 clusters introducing the intervention in that step (one CYL/cluster), as well as 66 youth comparisons for a 1:2 CYL: youth comparison ratio (i.e., 3 youth cohorts (one/Step) enrolling 33 CYLs:66 youth comparisons; in total, 99 CYLs and 198 youth comparisons enrolled). In each step, the CYLs will be enrolled in the evaluation and assessed as they are hired by NCHD, during the month before and first month of the step (i.e., in mos. 3–4 for Step 1, in mos. 10–11 for Step 2, and in mos. 17–18 for Step 3). The youth comparisons will be enrolled and assessed beginning the month before through the first 2 months of the step (i.e., in mos. 3–5 for Step 1, in mos. 10–12 for Step 2, and in mos. 17–19 for Step 3). Youth cohort participants will be followed up every 7 months. Given the context, some dropouts are expected, particularly among comparison youth. The sampling ratio of 2 comparison per 1 CYL is intended to compensate for these dropout levels. If a CYL drops out of the LEAPS program after having initiated her in-classroom teaching experience, she will be invited to remain in the evaluation as part of the CYL cohort. If a CYL drops out of the LEAPS program prior to completing her basic training (i.e., prior to having any in-classroom experience), she will be invited to remain in the evaluation as part of the comparison youth cohort. Similarly, if NCHD hires a comparison youth as a CYL, she will be invited to continue in the study as a CYL, and a new comparison youth will be identified and enrolled.

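### Youth are regrouped as CYL or comparison by events after enrolment, which can bias the Objective 2 contrast in a direction the protocol does not settle

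*Protocol article*

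**What the plan says.** The abstract states that "we will enroll three non-randomized youth participant open cohorts, one per step", and the Youth participants section says that "A case:comparison design will be employed in order to examine program impacts on youth participants". The planned size is "in total, 99 CYLs and 198 youth comparisons enrolled". On timing, "the CYLs will be enrolled in the evaluation and assessed as they are hired by NCHD", so a CYL is already in the cohort, with an enrolment assessment, before or around her basic training.

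The same section then sets three rules for women whose status changes:

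- Early leavers. "If a CYL drops out of the LEAPS program prior to completing her basic training", which the protocol equates with having had no classroom experience, "she will be invited to remain in the evaluation as part of the comparison youth cohort".
- Later leavers. "If a CYL drops out of the LEAPS program after having initiated her in-classroom teaching experience", she stays in the CYL cohort.
- Hired comparison youth. "if NCHD hires a comparison youth as a CYL, she will be invited to continue in the study as a CYL"; her former place is filled by another woman.

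The Impact evaluation section compares CYLs with comparison youth across follow-up. It takes account of how long CYLs were exposed and adjusts for age, schooling, marital status, household wealth and food insecurity. Its intent-to-treat statement is attached to the primary analysis, which concerns the child outcome. It names no youth analysis by group at enrolment.

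**The concern.** Leaving during training and being hired later are both events after enrolment, and both may be related to what is measured: autonomy, self-efficacy, professional growth, depressive symptoms and executive function. When such events decide the group, the contrast mixes any programme effect with the characteristics of the women who moved. The planned covariates describe demography and household circumstances. They do not capture motivation, ability or loss of family support. Accounting for length of exposure may help with a hired woman, but does nothing for an early leaver who is counted as unexposed.

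Two features make the early-leaver rule awkward. First, these women enter by being hired, not through the screening tool meant to make comparison youth a fair match. Second, some of them may have had part of the 12-day training, so the comparison group may contain partly trained women, which would dilute a true effect.

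The youth cohorts supply the quantitative comparison for Objective 2, which is worded as an evaluation of impact. A contrast that shifts with the grouping rule would weaken that claim.

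**Working it through.** **Stated figures.** Three cohorts of 33 CYLs and 66 comparison youth give 3 × 33 = 99 and 3 × 66 = 198, as the protocol says. It gives no dropout rate, number of movers, SD or target effect for youth, so everything below is an illustration on assumed inputs.

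**Set-up.** Units are SDs and the true programme effect is zero. R is the mean of CYLs who stay, L the mean of early leavers, H the mean of hired comparison youth, and C = 0 the mean of other comparison youth and of replacements. The same number n moves each way.

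- As enrolled (replacements left out): contrast = [(99 − n)R + nL]/99 − nH/198.
- Protocol grouping: contrast = [(99 − n)R + nH]/99 − nL/(198 + n).
- Shift = protocol grouping minus as enrolled.

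**Worked case**, n = 20, R = 0, L = −0.5, H = +0.5. As enrolled: −10/99 − 10/198 = −0.101 − 0.051 = −0.152. Protocol: 10/99 + 10/218 = 0.101 + 0.046 = +0.147. Shift +0.298.

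| R, L, H (assumed) | n each way | As enrolled | Protocol grouping | Shift |
|---|---|---|---|---|
| 0, −0.3, +0.3 | 10 | −0.045 | +0.045 | +0.090 |
| 0, −0.3, +0.3 | 20 | −0.091 | +0.088 | +0.179 |
| 0, −0.5, +0.5 | 10 | −0.076 | +0.075 | +0.150 |
| 0, −0.5, +0.5 | 20 | −0.152 | +0.147 | +0.298 |
| +0.3, +0.3, +0.3 | 10 | +0.285 | +0.286 | +0.001 |
| +0.3, +0.3, +0.3 | 20 | +0.270 | +0.272 | +0.003 |
| +0.3, +0.3, 0 | 10 | +0.300 | +0.255 | −0.045 |
| +0.3, +0.3, 0 | 20 | +0.300 | +0.212 | −0.088 |

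**What sets the sign.** For a few movers, one early leaver shifts the contrast by about (R − L)/99 − (L − C)/198 = (2R + C − 3L)/198, and one hired woman by about (3H − 2R − C)/198. The break-even for each is (2R + C)/3. Leavers below it, or hired women above it, move the contrast towards LEAPS; on the other side they move it against. With n each way the two add to about 3n(H − L)/198 = n(H − L)/66. The question is then whether hired women score above or below early leavers.

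**Scale.** With independent women and one assessment each, the standard error of a 99 versus 198 contrast is √(1/99 + 1/198) = 0.123 SD. A shift of 0.15 is about 1.2 standard errors, 0.30 about 2.4, and −0.09 about −0.7.

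**Levels versus change.** The table compares levels at one time. The plan links each woman's repeated assessments. If a mover's difference from her peers is the same at enrolment and at follow-up, it cancels in her change from enrolment and the shift goes to about zero. A bias on change needs movers whose trajectories differ.

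**The case against.** The strongest defence is that no randomization is broken. The youth cohorts are non-randomized by design, comparison youth are defined by having no LEAPS classroom experience, and the hypothesis concerns women who take part, so grouping by participation follows a stated definition. The outcomes are secondary and the child primary outcome is untouched. All of this stands, but it does not require hired women who left during training to be added to the comparison group, especially when the protocol keeps later leavers where they were.

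A reader might infer that the rule always favours LEAPS. The documents do not support that. The CYL recruitment section selects the highest workshop scorers, and the Youth participants section accepts that CYLs may be unusual among their peers. An early leaver from that group could score above the comparison mean and raise it. The last rows of the table show zero and negative shifts. Nothing says that early leavers are weaker or hired women stronger, although a woman hired through the same selection plausibly resembles other CYLs.

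Three further points stand. Later leavers staying in the CYL cohort is the conservative choice and confines the problem to the other two groups. The early-leaver window is short, since the training lasts 12 days, so 10 or 20 such leavers out of 99 may be too many. And the wording on hired youth looks forward: it does not say that their earlier data are relabelled, and together with the adjustment for exposure length it is compatible with a time-varying treatment. That part of the fix may already be intended.

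**Conclusion.** The point holds as a risk of bias of undetermined sign. Group membership depends on events after enrolment, the planned covariates would not remove the resulting selection, and no analysis by group at enrolment is named for youth. Bias towards LEAPS is plausible, conditional on leavers being weaker or less supported and hired women stronger.

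The size cannot be known from the protocol. The range of about −0.09 to +0.30 SD rests on 10 to 20 movers each way, mover means between −0.5 and +0.5 SD, no true effect, and a contrast of levels. Fewer movers, or stable differences analysed as change, would make it smaller. It is worth correcting because the remedy is cheap, but it bears only on secondary, non-randomized outcomes.

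**What to change.** In the main youth analysis:

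1. Keep every CYL who leaves before classroom teaching in the CYL group in which she was enrolled. This also places a woman who finishes training but never teaches, whom the present wording leaves unclear.
2. For a comparison youth who is hired, treat CYL status as a time-varying exposure: data before hire count as comparison, data after hire as CYL, with her last assessment before hire as baseline. Do not censor her at hire: if hired women are the stronger ones, censoring is informative and still removes them from the comparison group.
3. Adjust for the enrolment value of the outcome alongside the covariates already listed.
4. Report how many women move each way.
5. Keep the present grouping as an as-treated sensitivity analysis.

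The cost is wording plus a flag for original group and date of change; follow-up is unchanged. The downside is slight dilution of the estimate by early leavers. The change removes the shift caused by moving leavers and gives hired women a clean baseline. It does not remove the underlying selection of CYLs, which remains a limitation of the design.

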#### CYL recruitment

Following the TOT, district managers and FOs will initiate the CYL recruitment process in their catchment areas. NCHD will engage Feeder school teachers, community health workers, village leaders, and other community members to inquire about potential female youth candidates meeting the CYL recruitment criteria (i.e., aged 18 to 24 years old, have completed Grade 10 schooling, have their family’s support to participate). Candidates will be invited to attend a local CYL recruitment workshop. Recruitment workshops will be led by district managers and FOs, with support from LIST members, and comprise a range of activities designed to assess candidates’ literacy, numeracy, general knowledge, attitudes toward working with young children, problem solving, creativity, communication, and leadership potential. Youth participants’ performance on workshop activities will be scored using a standardized rubric. Participants who meet the CYL recruitment criteria and have the highest scores will be selected as the CYL.

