Youth comparisons will be identified using a screening tool during CYL recruitment activities and through door-to-door household visits. The screening tool for youth comparisons includes a series of questions and short case study exercises to ensure that the participant (i) meets the same gender, age, and education requirements as the CYL, (ii) has support from her family to pursue employment outside of the workplace (as is the case with CYLs), and (iii) demonstrates confidence, and advocacy and problem-solving skills. The tool takes approximately 15 min to implement. These screening criteria represent the qualities that the research team considers most central to the CYL role. Given that CYLs may be positive deviants in their community and have demonstrated high-selection workshop performance relative to their peers, the purpose of the screening tool is to ensure to the best of our ability that youth participants are a fair comparison for CYLs in terms of family environment and skillsets baseline.
Eligibility criteria:
◦ CYLs must be hired by NCHD.◦ Youth comparisons must be female, aged 18–24 years ± 2 weeks, have a minimum tenth grade education, have support from family members to pursue employment, meet capacity-checks for confidence, advocacy, and problem-solving skills, and have no in-classroom teaching experience with LEAPS.Exclusion criteria: Youth participant shows signs of severe clinical health condition or disability

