### Analysis

#### Impact evaluation

The primary analysis will use the intent-to-treat principle. Baseline balance will be tested between randomized groups to see whether randomization was successful. The primary outcome, IDELA total score, will be computed for each individual using the parameter estimates from the Graded Response Model, as recommended by the tool developers. We will assess the effect of the LEAPS intervention using the analytical framework proposed by Hussey and Hughes [71] for analysis of stepped wedge cluster-randomized trials. Estimation of treatment effects will be obtained from a generalized linear mixed model (GLMM) to produce the mean difference in IDELA scores for LEAPS intervention versus control. The GLMM will include a fixed effect for stratified randomization group, a random effect for cluster, a fixed effect for time, and use an exchangeable correlation structure. In addition, the study will perform a set of sensitivity analyses to explore potential deviations from the basic SW-CRT model proposed by Hussy and Hughes [71]. The closed school cohort data will be to examine the changes in the average school readiness among children participating in the LEAPS preschool between baseline and endline. Longitudinal data collected for school cohort participants will be linked using participant IDs. The preschool classroom structural and process quality data and the child household characteristics will serve as predictors of interest in adjusted analyses. Youth cohort data will be analyzed to examine differences in outcomes over time among CYLs as compared to the youth comparison group. Longitudinal youth participant data will be linked using participant IDs. Analysis will account for CYLs’ length of program exposure and adjust for potential confounding variables, including age, education, marriage status, assets-based household socio-economic status, and household food insecurity. No interim analyses are planned.

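### The minimum-level screen for comparison youth cannot by itself offset hiring CYLs by top rank, and the named youth covariates include neither the rubric score nor the enrolment outcome value

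*Protocol article*

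**What the plan says.** CYL recruitment: candidates attend a workshop that tests literacy, numeracy, problem solving, communication, leadership potential and related abilities. Their "performance on workshop activities will be scored using a standardized rubric", and "Participants who meet the CYL recruitment criteria and have the highest scores will be selected as the CYL".

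Youth participants: comparison women come by another route. "Youth comparisons will be identified using a screening tool during CYL recruitment activities and through door-to-door household visits". The tool confirms that each woman "meets the same gender, age, and education requirements as the CYL" and has family support. She must also "meet capacity-checks for confidence, advocacy, and problem-solving skills, and have no in-classroom teaching experience with LEAPS". The section names the selection problem openly: it says that "CYLs may be positive deviants in their community and have demonstrated high-selection workshop performance relative to their peers", and it offers the tool as the remedy, for family environment and for skills at baseline: "the purpose of the screening tool is to ensure to the best of our ability that youth participants are a fair comparison for CYLs".

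Analysis, Impact evaluation: youth outcomes are compared over time between the groups. The analysis allows for length of exposure and will "adjust for potential confounding variables, including age, education, marriage status, assets-based household socio-economic status, and household food insecurity".

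The Abstract describes the youth cohorts as non-randomized and says they are assessed at enrolment and every 7 months after that.

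**The concern.** The rubric decides who is hired, and its content lies close to the youth outcomes in Table 3: executive functions, self-efficacy, professional growth and aspirations. One group is the top of one scale; the other has cleared a threshold on a second scale. A threshold raises the average of the comparison group, but it does not bring that group to the level of women picked for ranking highest.

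The covariates that are named describe demographic and household circumstances, not ability. If women at the top of the rubric would have scored higher or developed faster without LEAPS, that difference would be read as programme impact, which is how the Objectives section frames the youth question.

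**Working it through.** The protocol gives no power, effect size or bias figure for youth, so there is none to reproduce. The cohort counts agree: 3 × 33 = 99 CYLs and 3 × 66 = 198 comparison youth.

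**1. The two routes side by side.**
- Instrument: workshop rubric for CYLs; screening tool for comparison youth.
- Rule: highest score for CYLs; capacity check for comparison youth.
- Source: workshop for CYLs; recruitment activities or household visits for comparison youth.
- Shared by both: gender, age, education and family-support requirements, and the enrolment assessment.

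**2. Detectable difference** (assumed: two-sided 5%, 80% power, one measurement, no dropout). (1.960 + 0.842) × √(1/99 + 1/198) = 2.802 × 0.1231 = 0.345 SD.

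**3. Rubric gap** (all inputs assumed). With k candidates per cluster, the expected top score in SD units is 0.56 (k = 2), 0.85 (k = 3) and 1.16 (k = 5). If a share p passes the screen, and the screen correlates r with the rubric, women who pass average r × φ(c)/p on the rubric, where c is the cut-off and φ the normal density.
- p = 75%: φ(c)/p = 0.424, giving 0.13 (r = 0.3) or 0.25 (r = 0.6).
- p = 50%: φ(c)/p = 0.798, giving 0.24 (r = 0.3) or 0.48 (r = 0.6).

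Gap = top score minus that mean: 0.08 to 0.44 (k = 2), 0.37 to 0.72 (k = 3), 0.69 to 1.04 (k = 5). With a single candidate the top score averages 0 and the gap turns negative, −0.13 to −0.48.

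**4. Bias without the enrolment value.** Multiply by an assumed rubric–outcome correlation of 0.2 to 0.5. For k = 2 to 5 the range is 0.2 × 0.08 = 0.02 to 0.5 × 1.04 = 0.52 SD.

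**5. Bias after adjusting for the enrolment value.** Assume a baseline–follow-up correlation of 0.6 and the same rubric correlation at both times. A fraction 1 − 0.6 = 0.4 remains, about 0.01 to 0.21 SD. The same adjustment lowers the detectable difference to 0.345 × √(1 − 0.6²) = 0.276 SD and the standard error to 0.1231 × 0.8 = 0.0985. At the upper end, 0.2/0.0985 = 2.03, so a comparison with no true effect would reach significance in CYLs' favour with probability about Φ(2.03 − 1.96) = 0.53. At the lower end the bias is negligible.

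**6. If the rubric predicts growth.** Suppose the comparison women were the next two on the rubric. The top score then exceeds their mean by 1.27, 1.03, 0.91 and 0.85 SD for 3, 4, 5 and 6 candidates. With an assumed correlation of 0.1 to 0.3 with later change, net of the named covariates, the bias runs from 0.1 × 0.85 = 0.085 to 0.3 × 1.27 = 0.38 SD of change. Adjusting for the enrolment value does not by itself remove this part.

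**The case against.** **The groups share a baseline.** Both are assessed at enrolment on the youth outcomes themselves, CYLs around the time of hiring and possibly at the recruitment workshop (Data collection procedures for youth participant assessments). The analysis looks at outcomes over time, so stable differences in level are not simply credited to LEAPS. This stands in large part. A reader might infer that the groups have no common early measure, or that comparability cannot be checked at all; the documents do not support either. The limit is timing: the setting may equally be a training session, and CYL enrolment runs into the first month of the step, so a measure before hiring and training is not assured. Differences in growth also remain.

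**Some comparison women may have rubric scores.** Those met at recruitment activities may have been scored; the article does not say. It would therefore be wrong to say that the rubric exists for CYLs only. Nor does the article say that the screen is stored only as pass or fail; that would be an inference from the eligibility wording.

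**The covariate list is open.** It is introduced by the word including, and a full analysis plan may add to it, so the article does not rule out further variables. But no later plan can adjust for a score that was not kept or not collected.

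**The protocol discloses the problem.** It does, and it claims fairness only as far as it can achieve it. It also provides for comparison youth being hired later, so they are not treated as unhireable. Disclosure does not make the remedy sufficient.

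**The magnitude is speculative.** This stands. Lack of an eligible candidate was a cluster exclusion criterion, so some candidate pools may be very small, and bounded scales or regression to the mean could reduce or reverse the bias. That the adjusted figures lie below the detectable difference is no reassurance, though: a bias smaller than the detectable effect can still shift the estimate and the error rate, as step 5 shows.

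**Conclusion.** The point holds in a limited form. The screen cannot by itself make comparison youth equal in skills to women hired for ranking highest, and the named confounders include neither the score that decided hiring nor the enrolment outcome. The shared enrolment assessment allows a partial check and a partial correction.

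The size of the bias is not known, and even its sign depends on assumptions about candidate numbers, the screen and the correlations. The illustrations range from negligible to about the detectable difference or somewhat above it; every input except the group sizes is assumed. Only the non-randomized secondary youth outcomes are affected; the randomized comparison of children's school readiness is not. This is an inexpensive improvement that should be made, not a fault that invalidates the trial.

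**What to change.** 1. Keep the existing rubric score for every enrolled woman who attended a workshop, in either group.
2. Record whether each comparison woman was found at a workshop or door-to-door.
3. Under Impact evaluation, name the enrolment value of the outcome as a covariate for all youth.
4. Add a sensitivity analysis in workshop attendees only, adjusting for both the rubric score and the enrolment value.
5. Optionally, in steps still to be rolled out, give CYL candidates the same screening tool and store its score for both groups.

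Items 1 to 4 cost one transferred score and one source field per woman, plus model wording. Item 5 takes 33 × 15 min = 8.25 h of assessor time per step for the hired CYLs (99 × 15 min = 24.75 h over all three steps), and more if every candidate takes it.

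Downsides: the workshop-only analysis has fewer comparison women, by a number the article does not allow one to estimate. The rubric score is missing for women found door-to-door, so it should not enter the full-cohort model, where missingness would follow group. CYLs in steps already rolled out would have no screening score.
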